### Schedule of assessment.

|                                                                      | Baseline | Week1 | Week2 | Week3 | Week4 | 3-month follow-up |
|----------------------------------------------------------------------|----------|-------|-------|-------|-------|-------------------|
| Sociodemographic and lifestyle questionnaire                         | X        |       |       |       |       |                   |
| 2016 American College of Rheumatology Diagnostic Criteria (ACR-2016) | X        |       |       |       |       |                   |
| Central Sensitization Inventory                                      | X        |       |       |       |       |                   |
| Pain Catastrophizing Scale                                           | X        |       |       |       | X     |                   |
| Beck Depression Inventory (BDI-II)                                   | X        |       |       |       | X     |                   |
| Pittsburgh Sleep Quality Index (PSQI)                                | X        |       |       |       | X     |                   |
| Outcomes                                                             | X        |       |       |       |       |                   |
| Brief Pain Inventory (BPI)                                           | X        | X     | X     | X     | X     | X                 |
| Patient Global Impression of Improvement (PGI-I)                     |          |       |       |       | X     |                   |
| Fibromyalgia Impact Questionnaire (FIQ)                              | X        |       |       |       | X     |                   |
| Conditioned Pain Modulation (CPM-test)                               | X        |       |       |       | X     |                   |
| Side effects of tDCS questionnaire                                   |          |       |       |       | X     |                   |

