## Statistical Analysis

Continuous and categorical variables were compared using Fisher's exact test, the chi-square test, and the t-test for independent samples. The Shapiro-Wilk normality test was applied to determine the normal distribution of continuous variables. A Linear Mixed-Effects Regression Models for Repeated Measure (LMM) assessed primary outcomes (pain severity and disability) with treatment, placebo response (responder vs. non-responder), time, and the treatment-by-time interaction as fixed effects, and included a random intercept for patients to account for time differences. If appropriate, we then performed the Bonferroni's Test adjustment for post hoc multiple comparisons to identify differences between the groups at each time point and used a paired t test to assess the effects on each experimental group. The Generalized Linear Model (GLM) was used to examine the treatment effect on the secondary outcomes including quality of life, HPT, PGI-I and the descending pain inhibitory system (DPIS). The treatment effect on primary and secondary outcomes was adjusted for analgesic use and placebo susceptibility. Analgesic use was included in the model to control a potential confounder affecting pain outcomes. This ensures that the observed effects of a-tDCS and s-tDCS are attributable to the interventions rather than variations in analgesic use, thereby enhancing the validity of the results. All analyses were adjusted for multiple comparisons using Bonferroni's Test. The modified ITT (m-ITT) analysis included those completing  $\geq 50\%$  of sessions, with missing data imputed using regression model coefficients. In the m-ITT, with an adjusted protocol, encompassing all patients who completed at least ten sessions. The choice of ten sessions for ITT was guided by most of the literature supporting clinical symptom improvement in chronic pain. This method is not as strict as classical ITT, but it suggests that A-tDCS could be useful in clinical settings with at least a minimum number of sessions. Specifically, we replaced missing values with imputed data derived from a regression model using observed data. The treatment group served as the predictor, and the outcome variable with missing values was imputed based on regression coefficients, indicating the relationship between the treatment group and the outcome. This imputation method was applied, for example, to ten patients who withdrew after ten tDCS sessions. Sensitivity analyses confirmed consistent LMM results with or without imputation ([see per-protocol analysis in results - Supplement II](#)).

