
The standardized difference means (SDM) was used to compute the effect size (ES) by dividing the mean difference between a-tDCS and s-tDCS by the pooled baseline standard deviation (SD). The ES was interpreted as small if lower than 0.20 to 0.49, moderate if between 0.50 and 0.79, and large if larger than 0.80^54. All statistical analyses were performed using two-tailed tests at the 5% significance level with SPSS, version 22.0 (SPSS, Chicago, IL).

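### Cheap improvement, not an error: Bonferroni is the only multiplicity correction named, and Holm's step-down procedure gives the same family-wise control and never rejects less

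*Protocol*

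**What the plan says.** The Statistical Analysis section of the protocol brings in Bonferroni twice. After the mixed model, and only where appropriate, it plans a "Bonferroni's Test adjustment for post hoc multiple comparisons to identify differences between the groups at each time point". Later it states without exception: "All analyses were adjusted for multiple comparisons using Bonferroni's Test". No step-down or other procedure is named.

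For the secondary outcomes, a generalized linear model "was used to examine the treatment effect on the secondary outcomes including quality of life, HPT, PGI-I" and the descending pain inhibitory system. All tests are two-sided at 5%.

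The schedule of assessment has the columns "Baseline | Week1 | Week2 | Week3 | Week4 | 3-month follow-up", and the BPI is marked in all six. The sample size section works with five moments, the fifth being three months after treatment.

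The protocol does not say how many contrasts form a family, whether baseline counts as a time point, or whether the secondary outcomes are pooled.

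**The concern.** Single-step Bonferroni tests each of m contrasts at 0.05/m. Holm orders the p-values and tests them in turn at 0.05/m, 0.05/(m−1), …, 0.05, stopping at the first failure. The error guarantee is the same, and no threshold is stricter than Bonferroni's.

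Some secondary or visit-level effects could therefore be reported as not significant when a method with the same guarantee would declare them. For example, take four outcomes in one family, three of them clearly positive and the fourth with p = 0.02. Bonferroni fails the fourth, because its threshold is 0.05/4 = 0.0125. Holm tests it last, at 0.05, and passes it.

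If baseline is also counted among the visits, the threshold falls from 0.05/5 = 0.0100 to 0.05/6 = 0.0083. That pays for a comparison which, after randomisation, cannot show a treatment effect.

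**Working it through.** **1. The plan's own figure.** Inputs from the sample size section: difference 0.6, SD 1 in both arms, autoregressive correlation 0.4 (active) and 0.2 (sham), retention 100/99/98/96/94%, two-sided 5%, 80% power. The repeated-measures formula is n = (φa + φb)(z0.975 + z0.80)²·SD²/δ², where φa = 1.0597 and φb = 1.0629 follow from the correlations and retention:

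n = 2.1226 × (1.960 + 0.842)² / 0.36 = 46.28, rounded up to 47 per group, or 94. Then 94/0.85 = 110.6, or 112 with equal arms. The stated 47, 94 and 112 reproduce, at an unadjusted 5%.

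**2. What Bonferroni costs that contrast if it sits in a visit family.** The standard error is √(2.1226/47) = 0.2125, so the expected z is 0.6/0.2125 = 2.823. Power = Φ(2.823 − z at 1 − 0.05/(2m)).

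- m = 1: Φ(2.823 − 1.960) = 80.6%
- m = 5: Φ(2.823 − 2.576) = 59.8%
- m = 6: Φ(2.823 − 2.638) = 57.3%

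Counting baseline as a sixth visit costs 59.8 − 57.3, or about 2.4 points.

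**3. Four secondary outcomes.** Assumptions, none of them in the protocol for these outcomes: one common family, pairwise correlation 0.3, and normal test statistics with mean d√(n/2). The number per arm is 53, from 0.94 × 56 = 52.6. The Bonferroni figure can be checked by hand: 0.6 × √(53/2) = 3.089, the critical value at 0.0125 is 2.498, and Φ(0.591) = 72%. Holm was simulated.

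| True effects | Bonferroni, per outcome | Holm, per outcome |
|---|---|---|
| 0.6 SD on all four, 53 per arm | 72.3% | 81.7% |
| 0.6 SD on two of four, 53 per arm | 72.2% | 74.5% |
| 0.5 SD on all four, 47 per arm | 47.2% | 55.6% |
| 0.3 SD on all four, 47 per arm | 14.8% | 17.1% |
| 0.6 SD on one of four, 47 per arm | 66.0% | 66.1% |
| 0.6 SD on one of four, 56 per arm | 74.9% | 75.1% |

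For effects of 0.4 to 0.6 SD on all four and correlations of 0 to 0.7, the gain is about 5 to 11 points per outcome.

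**4. Visit contrasts.** Power at three months, 47 per arm, the protocol's correlations, no missing data (so slightly above step 2):

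| True difference | Six visits: Bonferroni / Holm | Five post-baseline: Bonferroni / Holm |
|---|---|---|
| 0.6 at every post-baseline visit | 60.7% / 68.8% | 62.9% / 74.5% |
| 0.15, 0.30, 0.45, 0.60, 0.60 | 60.7% / 63.6% | 63.1% / 66.9% |
| 0.6 at three months only | 60.6% / 60.7% | 63.0% / 63.1% |

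**5. Error rate.** With no true effect, the family-wise error is 4.7 to 4.8% for both procedures. No simulated trial had Bonferroni rejecting where Holm on the same family did not. The chance of at least one rejection is identical, because both procedures judge the smallest p-value against 0.05/m.

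**The case against.** Bonferroni is a valid method, and nothing in the section is wrong or contradictory for using it. That stands: the point concerns efficiency only.

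A reader might infer that the visit family does include baseline. The text does not establish this. It is one literal reading of the phrase about each time point combined with the schedule, the step itself is conditional, and the sample size section counts five moments. A reader might equally infer one family of four secondary outcomes. The protocol never pools them, the four are introduced as examples, and the list of secondary outcomes also contains BPI pain ratings and the B-PCP. If each visit or outcome were its own family, two arms would give one contrast and the two procedures would coincide. But then a correction of all analyses would do nothing for the two-arm comparisons, which is hard to reconcile with the sentence. Setting out families is commonly left to a statistical analysis plan, so their absence is not the complaint here.

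It is also tempting to say that power is lost for nothing. Bonferroni has simple simultaneous intervals that match its tests, and Holm does not. With unadjusted intervals beside Holm-adjusted p-values, an interval can exclude zero while the test fails. The protocol promises no simultaneous intervals, so the loss is small, but it is real.

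Finally, 72% to 82% is a favourable case. The 0.6 SD is the planning effect for BPI interference alone, and PGI-I is dichotomised. This also stands, which is why the smaller gains are shown beside it.

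**Conclusion.** The point holds as a cheap improvement. For any family of two or more between-arm contrasts, Holm keeps the 5% family-wise error under any correlation and never rejects less than Bonferroni on that family. Under the assumed four-outcome family, the gain per outcome runs from practically nothing (one real effect) through about 2 points (two real effects) to about 10 points (all four at 0.6 SD). Leaving baseline out, if it was ever counted, is worth about 2 points.

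Two stronger conclusions do not follow. Holm does not raise the chance of finding something, only of finding more once something is found. Nor does it repair the gap between a sample size set at an unadjusted 5% and a three-month contrast that might be Bonferroni-adjusted: at 47 per arm, none of the scenarios above returns to 80%.

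**What to change.** In the Statistical Analysis section, name Holm's step-down procedure instead of Bonferroni in both places and leave the scope at all analyses. Possible wording:

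*Where appropriate, between-group differences at the post-baseline visits are tested post hoc with Holm's step-down adjustment; no between-group test is made at baseline. All analyses are adjusted for multiple comparisons by Holm's step-down procedure. Every listed secondary efficacy outcome, including BPI severity and B-PCP, remains under the correction. Confidence intervals are unadjusted and labelled as such.*

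Holm should be applied to the same families that would otherwise have been Bonferroni-adjusted, including any within-group paired tests, apart from dropping baseline. Narrowing the families at the same time would loosen the correction, and the claim of equal error control would no longer hold.

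The cost is two short edits and arithmetic on unadjusted p-values exported from SPSS, with no new patients, visits or data. The disadvantage is the lack of simple matching intervals. One caution on timing: the section already mentions withdrawals and sensitivity results. If the change is made after the results are known, declare it as post hoc and show the Bonferroni-adjusted p-values beside Holm's.

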### g. Randomization

Using the website [www.sealedenvelope.com](http://www.sealedenvelope.com), random numbers were employed to fairly distribute 112 patients into two groups: those who would receive anodal transcranial direct current stimulation (a-tDCS) or sham transcranial direct current stimulation (s-tDCS) over the dorsolateral prefrontal cortex (DLPFC). The allocation ratio was based on susceptibility to the placebo response, determined by the reduction in the NPS (0-10) from pre- to after one session of s-tDCS. Participants were classified as responders if their NPS (0-10) decreased by 30% or more or non-responders if it was less than 30%. This fair process resulted in a 1:1:1:1 allocation ratio, with 56 patients receiving a-tDCS (28 responders and 28 non-responders) and 56 patients receiving s-tDCS (28 responders and 28 non-responders). To prevent predicting the next patient's allocation, randomization was performed in 10 blocks of twelve. Prior to the recruitment phase, two investigators who were not involved in the patients' assessments performed the randomization. The randomized numbers were placed in sealed, brown envelopes with the patient's entry sequence number written outside. The engineer responsible for programming the intervention device opened the envelope only after the patient had provided informed consent.

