### **Secondary Outcomes:**

- ii. The Brief Pain Inventory (BPI) assesses pain at its “worst,” “least,” “average,” and “now” (current pain) on a 0–10 numerical rating scale, where 0 indicates no pain and 10 represents the worst pain imaginable. This assessment was conducted weekly during treatment and three months after treatment completion. These single-item measures are supported by IMMPACT recommendations for pain assessment in clinical trials  and the FDA Draft Guidance for Patient-Reported Outcome Measures .
- iii. The Brazilian Profile of Chronic Pain: Screen (B-PCP) identifies the individual's multidimensional pain experience across three domains: pain severity (0-32), disability (0-36), and emotional burden (0-25). Higher scores indicate

- greater disability or emotional distress, with a total score ranging from 0 to 93 points. Changes from baseline to the end of treatment and at three months follow-up will be analyzed.
- iv. Fibromyalgia Impact Questionnaire (QIF): Measures the impact of fibromyalgia on quality of life across three domains: function (9 questions), overall impact (2 questions), and symptoms (10 questions). Scores are weighted differently, with a maximum total score of 100 .
  - v. Patient Global Impression of Improvement (PGI-I): A 7-point scale assessing patients' perceptions of symptom improvement post-treatment, ranging from "very much worse" (1) to "very much improved" (7) . Impressions were categorized into "improved" or "very much improved" versus "very much worse" to "slightly improved".
  - vi. Quantitative Sensory Testing (QST) is a standardized protocol using a computer Peltier-based device thermode (measuring 30X30mm), which was attached to the skin on the ventral aspect of the mid-forearm. The temperature was set at 32OC and increased at a rate of 1 OC/s until it reached a maximum of 52Oc. Each participant was instructed to push the button when the stimulation became painful. To determine the heat pain threshold, each patient's threshold was measured three times, with a 40-second break between each assessment. The average of the three assessments was used to define the heat pain threshold for each patient .

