  - vii. The endogenous pain modulatory system (EPMS) function was assessed through a conditioned pain modulation (CPM) test using a computerized thermode, like the one used to determine the heat pain threshold (HPT). Initially, on the non-dominant forearm, three quantitative sensory testing (QST) assessments were conducted with a 40-second interval between stimuli. Each participant was instructed to press a button when their numerical pain score (NPS, 0-10) reached 6/10. The average temperature of the test stimulus was recorded as T0. After five minutes, participants immersed their dominant hand up to the wrist in water at a temperature of 0°C–1°C for 15 seconds. The QST was then reassessed, resulting in a pain score NPS(T1) based on the evoked pain from the thermode using the T0 temperature on the ventral non-dominant forearm. The CPM test score was calculated as the difference between NPS(T1) and NPS(T0). A negative CPM score indicates proper EPMS function, while a score of  $\geq 0$  indicates impaired function.
  - viii. Side effects of tDCS were evaluated using the Systematic Assessment for Treatment Evaluation questionnaire.
  - ix. Adherence to the protocol was assessed by the record in the tDCS device, which registers impedance, resistance, time of use, and duration of each session. This data was downloaded at the end of the treatment.

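### The Bonferroni rule covers every analysis, with no stated family and no exemption for side effects, so as written it can make a real excess of harm easier to miss

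*Protocol*

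**What the plan says.** The Statistical Analysis section mentions Bonferroni twice. The first mention is conditional and concerns post hoc comparisons of the arms at each visit in the mixed model. The second comes after the models for the secondary outcomes and the covariate adjustment, and it is unconditional: "All analyses were adjusted for multiple comparisons using Bonferroni's Test". Neither mention gives a family or a number of comparisons. The section closes with "All statistical analyses were performed using two-tailed tests at the 5% significance level".

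Under the heading "Secondary Outcomes", item viii reads: "Side effects of tDCS were evaluated using the Systematic Assessment for Treatment Evaluation questionnaire". The Schedule of assessment has a row "Side effects of tDCS questionnaire", marked at week 4 only.

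No test is described for side effects specifically. The generalized linear model is assigned to "secondary outcomes including quality of life, HPT, PGI-I and the descending pain inhibitory system (DPIS"; side effects are not named there, although the list is introduced as non-exhaustive. The general opening sentence, "Continuous and categorical variables were compared using Fisher's exact test, the chi-square test, and the t-test for independent samples", supplies the methods that a comparison of symptom frequencies would ordinarily use. The Randomization section plans 56 patients per arm.

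**The concern.** Bonferroni limits false positive claims. For efficacy that is the cautious direction. For harms the costlier error is to miss a real excess, and a stricter threshold makes that error more likely. A rule that covers every analysis, in a protocol that lists side effects among its secondary outcomes, carries the efficacy safeguard over to safety.

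The device is self-applied at home and there are 56 patients per arm, so power to detect a moderate excess of a symptom is limited even at 5%. If an adjusted, non-significant result were then taken as evidence that the arms are equally safe, the conclusion would rest partly on the threshold. The primary result is not affected.

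**Working it through.** **Inputs from the protocol.** 56 patients per arm (Randomization); two-sided 5% level and Bonferroni on all analyses (Statistical Analysis); side effects as item viii of a list of secondary outcomes that runs from ii to ix, which is 8 items.

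**Inputs assumed.** The protocol gives no expected symptom rates and no family size k. Both are varied below.

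**The plan's own figure.** The protocol states no power for side effects. Its only sample-size figure is for pain interference. The repeated-measures formula, with five time points, autoregressive correlations 0.4 and 0.2, the stated retention, SD 1 and difference 0.6, is n = (φa + φb)(1.960 + 0.842)² / 0.6². It gives 46.3, so 47 per arm and 94 in total. Allowing for 15% dropout, 47 / 0.85 = 55.3, so 56 per arm and 112 in total. Both figures reproduce, so 56 per arm is used here.

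**Formula for side effects.** Two-proportion test with pooled variance, n per arm, at level α = 0.05/k:

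power = Φ[(|p1 − p2| − z(1−α/2) × s0) / s1], where s0 = √(2p̄(1−p̄)/n) and s1 = √(p1(1−p1)/n + p2(1−p2)/n).

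**Worked case, 40% against 20%.** p̄ = 0.30, s0 = √(2 × 0.30 × 0.70 / 56) = 0.0866, and s1 = √((0.24 + 0.16) / 56) = 0.0845.

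- k = 1: z = 1.960; (0.20 − 0.1697) / 0.0845 = 0.358; power 64%.
- k = 2: z = 2.241; (0.20 − 0.1941) / 0.0845 = 0.070; power 53%.
- k = 5: z = 2.576; (0.20 − 0.2231) / 0.0845 = −0.273; power 39%.
- k = 10: z = 2.807; (0.20 − 0.2431) / 0.0845 = −0.510; power 31%.

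**Other assumed rates, same formula.**

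| Active vs sham | k = 1 | k = 5 | k = 8 | k = 10 |
|---|---|---|---|---|
| 40% vs 20% | 64% | 39% | 33% | 31% |
| 30% vs 10% | 76% | 53% | 46% | 43% |
| 50% vs 25% | 79% | 56% | 50% | 47% |
| 60% vs 30% | 90% | 74% | 68% | 66% |

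**Share of power kept.** For 40% vs 20%: 0.528/0.640 = 82% at k = 2, 0.392/0.640 = 61% at k = 5, and 0.305/0.640 = 48% at k = 10. For 30% vs 10%: 0.529/0.761 = 70% at k = 5 and 0.434/0.761 = 57% at k = 10. For 50% vs 25%: 0.564/0.788 = 72% and 0.469/0.788 = 60%. For 60% vs 30% at k = 8: 0.684/0.902 = 76%.

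**Exact test.** The protocol also names Fisher's exact test, which gives lower power throughout. For 40% vs 20% it is 57% unadjusted and 28% at k = 8.

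**If the rule applies only within one outcome.** A single two-arm comparison at week 4 has k = 1, and nothing is lost.

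**The case against.** The strongest reply is that the broad reading is not the intended one. The unconditional sentence follows a run of text on treatment-effect models for pain and related outcomes, and the first Bonferroni sentence says what is adjusted: arm comparisons across visits within an outcome. On that view side effects, collected once in two arms, carry no penalty. This is a fair account of what the authors may have meant, and it sets the lower end of the loss at nil. It does not settle the matter. The visit-by-visit comparisons already have their own sentence, the second is worded to reach everything, and nothing narrows it or exempts safety.

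A second reply is that no test of side effects is described: the model sentence does not name them, and the shorter secondary-outcome lists under the two objectives headings omit them. That stands. A reader might infer that the protocol plans adjusted significance tests symptom by symptom, so that each further questionnaire item raises the bar. The document does not support this. It neither makes the questionnaire items the family nor says how many there are. The family could equally be the eight listed secondary outcomes, in which case the number of symptoms would not matter. The layout of safety tables may also properly be left to a statistical analysis plan. The blanket rule, however, is stated in the protocol itself.

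A third reply is that nothing in the protocol says a non-significant result would be read as no difference. That is correct. The misreading is a risk to guard against, not a stated intention.

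**Conclusion.** The point holds as a minor fault of wording. The Bonferroni sentence has no defined family and no exemption for safety, and side effects are a listed secondary outcome, so any comparison of them between arms can fall under a stricter threshold.

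The size is conditional. At 56 per arm and 40% against 20%, power goes from 64% to about 53%, 39% or 31% for families of 2, 5 or 10. These figures rest on assumed symptom rates, an assumed family, an actual significance test on side effects, and the normal approximation.

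A reader might infer that the rule halves the trial's ability to see harm. The figures do not support that as a general statement. Among the first three rate pairs with families of 5 and 10, only one of six cases, 40% vs 20% with a family of 10, loses about half its power. The loss is about a quarter at a family of 8 when unadjusted power is near 90%, and there is none on the within-outcome reading.

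**What to change.** Reword the sentence so that Bonferroni applies to efficacy comparisons only, and name those comparisons so that the family is defined. Add that side effects will be reported by arm as counts and percentages, with risk differences and unadjusted 95% confidence intervals, and that a non-significant difference will not be taken as evidence of equal safety.

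The cost is a sentence or two. No data collection changes and the primary analysis is untouched. The small downside is that, without adjustment, an occasional symptom will differ between arms by chance and must be read with care.

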### ***HB-tDCS Sessions and Compliance Monitoring***

To ensure compliance with protocol during HB-tDCS sessions, we implemented several procedures:

- (i) Participants were advised to choose a quiet and suitable time in their daily schedule for their treatment session.
- (ii) The initial home-based session was conducted under remote supervision, allowing participants to seek assistance from the research team if needed.
- (iii) A weekly contact through WhatsApp to track participants' progress and ensure they adhered to the treatment protocol.
- (iv) Participants were encouraged to contact the research team for assistance.
- (v) Participants were instructed to promptly document any adverse effects in a diary following each tDCS home session.

To verify the adherence to the following protocol, a biomedical engineer reviewed the records to confirm the session time, duration, current intensity, and contact impedance. The average impedance was employed to assess the quality of the delivered current. The impedance should range between 8 and 4 k $\Omega$  at the beginning of stimulation, with the target during treatment between 3 and 2 k $\Omega$ . For a valid 20-minute a-DCS session, impedance levels should be between 3 and 2 k $\Omega$  for at least half the time in the case of a duration of 10 min. The literature supports the choice of a 10-minute duration by demonstrating its effectiveness in promoting neuroplasticity, with studies by Nitsche (2000)  and Bikson (2016)  adding to this understanding.

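### The ten-session analysis set and arm-based imputation are not limited to efficacy, so read literally they also govern tDCS side effects and can understate harm if stopping is related to harm

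*Protocol*

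**What the plan says.** Under Secondary Outcomes in the Protocol, item viii reads: "Side effects of tDCS were evaluated using the Systematic Assessment for Treatment Evaluation questionnaire". The Schedule of assessment marks the row "Side effects of tDCS questionnaire" at Week 4 only. A second source is collected as treatment goes on. Under HB-tDCS Sessions and Compliance Monitoring the Protocol says: "Participants were instructed to promptly document any adverse effects in a diary following each tDCS home session".

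The Statistical Analysis section defines one analysis set. It begins "The modified ITT (m-ITT) analysis included those completing" at least 50% of sessions, and then restates the rule: "In the m-ITT, with an adjusted protocol, encompassing all patients who completed at least ten sessions". The stated reason for ten sessions is literature on symptom improvement in chronic pain. Missing data are handled by one rule: "Specifically, we replaced missing values with imputed data derived from a regression model using observed data". The only predictor named is the arm: "The treatment group served as the predictor, and the outcome variable with missing values was imputed based on regression coefficients". The section reports that this was done, for example, for ten patients who withdrew after ten sessions. A per-protocol sensitivity analysis is mentioned but not defined. Neither side effects nor the diary is named in the section, and no sentence limits the set or the imputation to efficacy outcomes.

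**The concern.** A minimum number of sessions is an efficacy device: it asks what happens in people who received enough treatment to respond. For harms the same threshold selects on tolerability. Someone who stops at session four because of a scalp reaction to self-applied stimulation is a person the harm comparison needs, and the only defined set leaves that person out. The Study Discontinuation Criteria raise the same issue. Participants with emerging suicidal ideation or (hypo)manic episodes leave the study whenever this occurs, and if that is before session ten the defined set omits them as well.

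The imputation rule adds a second problem. The questionnaire comes once, at Week 4, so a participant who leaves after session ten without completing it has a missing value. With arm as the only named predictor, that value becomes the mean of the arm members who stayed. For a yes/no side effect this is a fraction, not an event.

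What is at stake is the active-versus-sham comparison of side effects for a device used at home. Diary and device-log data that could cover early stoppers are already collected.

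**Working it through.** **Inputs from the Protocol.** 112 participants, 56 per arm (Randomization). This follows from the sample size section: 47 per arm, and 47/0.85 = 55.3, rounded up to 56. The 47 also reproduces: the repeated-measures formula with the stated correlations and retention gives 46.28 per arm. No harm rate is stated anywhere, and none of these figures decides the point.

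**How many could lack a Week 4 questionnaire.** The Protocol gives only indirect guides:
- Ten withdrawals after ten sessions: 10/112 = 8.9% of those randomised, split by arm not given.
- The 15% dropout allowance: 0.15 × 56 = 8.4 per arm, covering the whole study.
- Planned retention of 99% and 98% at moments 2 and 3: 0.56 and 1.12 per arm lost.

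**Formula.** In one arm let n be the number randomised and treated, and k the number without a questionnaire (dropped if under ten sessions, imputed if ten or more). Let p0 be the harm rate in those observed and q the rate in the k.
- Rate under the written rules: p0. Dropping leaves p0, and filling in the arm mean also leaves p0.
- Rate in all treated: p0 + (k/n)(q − p0).
- Understatement: (k/n)(q − p0). It is zero when q = p0.
- Change in the active-sham difference: active understatement minus sham understatement. It is zero when the two are equal, and it has the opposite sign when the sham arm's is larger.

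**One arm, n = 56, p0 = 20% (assumed).**

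| Stop before ten | Withdraw after ten | k | q | All treated | Written rules | Understatement |
|---|---|---|---|---|---|---|
| 2 | 0 | 2 | 100% | 22.9% | 20.0% | 2.9 points |
| 5 | 5 | 10 | 20% | 20.0% | 20.0% | 0 |
| 5 | 5 | 10 | 50% | 25.4% | 20.0% | 5.4 points |
| 5 | 5 | 10 | 100% | 34.3% | 20.0% | 14.3 points |

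For the third row: (46 × 0.20 + 10 × 0.50)/56 = 14.2/56 = 25.4%. Over p0 from 10% to 30%, 2 to 8 early stoppers, 0 to 5 later withdrawals and q from p0 to 100%, the understatement runs from 0 to (13/56)(1.00 − 0.10) = 20.9 points.

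**Two arms, assumed counts, chosen to show the mechanism.**
- Suppose 12/56 active and 3/56 sham participants have a reaction: 21.4% vs 5.4%, difference 16.1 points, two-sided Fisher p = 0.024. If 6 and 1 of them stop before session ten, the ten-session set shows 6/50 vs 2/55: 12.0% vs 3.6%, difference 8.4 points, p = 0.147.
- Check by the formula: active (6/56)(1 − 0.120) = 9.4 points; sham (1/56)(1 − 0.036) = 1.7 points; 9.4 − 1.7 = 7.7, which is 16.1 − 8.4.
- Suppose 6/56 active and 0/56 sham participants have a reaction (p = 0.027) and all 6 stop early. The ten-session set shows 0/50 vs 0/56.

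**The case against.** The strongest answer is that the Statistical Analysis section never says these rules apply to side effects. The outcomes it names are pain severity, disability, quality of life, heat pain threshold, global impression and descending inhibition. Its reason for ten sessions concerns efficacy, and its sensitivity check concerns the mixed-model results. The secondary-outcome lists in the two objectives sections omit side effects. The Secondary Outcomes heading also covers adherence, to which a ten-session rule could hardly be meant to apply. The section's opening sentence offers Fisher and chi-square tests without tying them to any set. All of this stands, so the application to harms is a literal reading and not a stated rule. But the list of secondary outcomes for the generalized linear model opens with the word including, the section speaks of primary and secondary outcomes together, and nothing exempts an item listed as secondary.

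It is also fair that a safety set and diary tables are usual content of a statistical analysis plan, which is not shown. Their absence alone is no finding. The point is that the Protocol already fixes a set and an imputation rule, and they do not suit harms.

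A reader might infer that recorded harms are overwritten. They are not: the text says "we replaced missing values with imputed data derived from a regression model using observed data", so a diary entry is left out, not replaced. A reader might also take the Protocol's description of minimal risk as resting on this comparison. It rests on earlier studies in home settings.

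Finally, the two-arm examples need 6 of 56 active participants to stop early because of harm. Nothing in the Protocol supports that number, and the planned early retention suggests fewer.

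**Conclusion.** The point holds in a limited form. Followed literally, the written rules condition the side-effect comparison on having had at least ten sessions, and they give later withdrawals without a questionnaire the mean of those who stayed. This can understate harm within an arm, by (k/n)(q − p0). It can shrink the active-sham difference only if harm-related stopping is more marked in the active arm.

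A reader might infer that the plan necessarily understates harm or always biases the comparison toward no difference. The Protocol does not support that, since it gives neither harm rates nor reasons for stopping by arm. If stopping is unrelated to harm the bias is nil. If it is related but equal in both arms, the difference is unaffected. In the assumed one-arm range the understatement runs from 0 to about 21 points. With only 2 early stoppers, no later withdrawals and a 20% observed rate, it is at most 2.9 points. The change is worth making because it is cheap and removes the dependence on tolerability, not because a particular bias has been shown.

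**What to change.** State in the Statistical Analysis section that the ten-session set and the regression imputation apply to efficacy outcomes only. For side effects, specify:
- all randomised participants who received at least one session, grouped by the stimulation actually programmed;
- no imputation;
- the per-session diary used together with the Week 4 questionnaire;
- by arm, the number with each effect and the number who stopped because of an adverse effect, with 95% intervals. Device logs give the sessions delivered, if a rate per session is wanted.

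The ten-session set can stay as a supporting display.

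The cost is a few sentences and one table from data already collected, with no extra visits or procedures. The drawbacks are that diaries of early stoppers may be incomplete, which should be reported, and that the harm rates may be slightly less favourable. The change concerns analysis only and alters nothing in clinical management.
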